#### Maintenance

The maintenance of reported changes in physical activity, self-efficacy, and HRQOL for participants in the intervention arm will be evaluated after 24 weeks with the same assessment tools. Participants will not have access to their previous scores.

Participants will be informed that they can withdraw from the study at any time by contacting the principal investigator. In such cases, the reason for withdrawal from the study will be ascertained and recorded. Nonresponders to the questionnaire will be followed up by email to record their reasons for dropping out of the study.

#### Process Evaluation

Use of each component of the revised Move More Pack will be assessed using a 4-point Likert scale of often, sometimes, rarely, and never. The 4-point Likert scale is included as part of the questionnaire administered to the intervention arm at 12 weeks and the control arm at 24 weeks. Participants will also have the opportunity to add comments about their use and their perceived usefulness of the revised Move More Pack. At the 12-week time point, participants from the intervention arm will be stratified into two groups, those inactive before diagnosis and those moderately active or active before diagnosis. Five participants from each group will be randomly selected and interviewed by phone to gain a deeper understanding of their interaction with, and views of, the revised Move More Pack. This interview process is repeated in the control arm at 24 weeks.

Interviews will follow a semistructured format and will be conducted by the principal investigator. This format has been selected to ensure that data are collected on central topic areas of use and perceived usefulness of the components of revised Move More Pack while not restricting the flow of the conversation. In addition, the interviews will aim to gather data to situate the experience of using the revised Move More Pack within a broad social context. The interview topic guide is included as Multimedia Appendix 8.

### Data Analysis

The quantitative data will be analyzed using intention-to-treat analysis. The GLTEQ provides a physical activity score, and these scores can be used to categorize participants into inactive, moderately active, and active groups. The two-proportion *z* test is used to investigate differences between the proportions of participants in the control arm and the intervention arm classified as active.

Secondary analysis of the paired before and after ordinal data within each intervention arm will be analyzed with the Wilcoxon’s signed-rank test; across arms, comparisons will be analyzed with the Mann-Whitney *U* test. The mean GLTEQ scores will be analyzed with the independent *t* test and the paired *t* test. The predictors of self-efficacy and prediagnosis physical activity on post-intervention physical activity levels will be assessed by multiple regression analysis. Additional quantitative data will include descriptive statistics such as means, standard deviations, medians, and percentages.

The interviews will be recorded and transcribed verbatim. The interview transcripts and the qualitative comments made by the participants as part of the questionnaires administered at the 12-week and 24-week time points will be thematically analyzed [61] by two of the study investigators, ensuring that identified themes are grounded in the original data. A third investigator will be used where there are differences in opinion. The process of analysis will follow five stages:

Familiarization with the data involving reading and rereading the interview transcripts and qualitative comments.Initial coding.Theme identification.Theme review and development of higher level categories.Identification of relationships and patterns.

The investigators will move back and forth through these steps until they concur and are satisfied with the themes, categories, relationships, and patterns identified.

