### Sample size

NHS England [13] report that 23% of cancer survivors are active to the recommended levels for aerobic activity, 31% are inactive, and 46% are physically active but not to the recommended levels. NHS England [13] also reported that 18% of cancer survivors are interested in becoming more active. The sample size for this study has been calculated based on the assumption that the revised Move More Pack will increase the proportion of the sample achieving the aerobic physical activity guidelines by 18%. A sample of 82 participants will be required per arm for a one-tailed test, power of 80% with alpha set at 5%. A total of 99 participants will be recruited per arm to allow for a 20% dropout.

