### Procedures and Assessment Tools

#### Effectiveness

Physical activity will be assessed using the GLTEQ, a reliable and validated tool [43] used previously with cancer survivors [57]. The cancer specific 7-item Functional Assessment of Cancer Therapy Questionnaire (FACT-G7), also a reliable and validated tool, will be used to assess HRQOL [58].

The GLTEQ and the FACT-G7 will be administered electronically at baseline in the intervention and control arms of the study. Participants will be asked to complete the GLTEQ twice:

To consider their levels of activity in a standard week before their cancer diagnosis, to allow for the tailoring of the e-newsletters, and to provide a context for the use of the revised Move More Pack.To consider their levels of activity in a standard week after diagnosis, as a baseline assessment of physical activity.

Self-efficacy will be assessed using the following single-item assessment tool: “On a scale of 1 to 10 (1=not at all confident and 10=very confident), how confident are you that you will be physically active in situations such as the following: feeling tired, bad mood, not having the time, on vacation, bad weather?” A similar measure has been used previously with cancer survivors [59]. A single-item assessment tool is selected for its practical application to a real-world setting, and furthermore, single-item assessment tools can perform just as well as multi-item assessment tools [60].

Additional participant information will be collected on date of birth, gender, primary cancer site (type), time since diagnosis, treatment received, time since completion of treatment, response to treatment, and ethnic group. The structure of these questions is that used by NHS England [13]. These questionnaires and participant data will be collected using software from Qualtrics, USA.

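### No between-arm test is stated to adjust for the baseline values the trial collects, and within-arm significance tests sit alongside; a baseline-adjusted estimate should carry the 12-week conclusions

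*Protocol article*

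**What the plan says.** The article names its tests under Data Analysis. For the proportion active, the two-proportion z "test is used to investigate differences between the proportions of participants in the control arm and the intervention arm classified as active". As secondary analysis, the "paired before and after ordinal data within each intervention arm" go to the Wilcoxon signed-rank test, and "across arms, comparisons will be analyzed with the Mann-Whitney" U test. Mean GLTEQ scores get an independent t test between arms and a paired t test within arms. The one regression relates self-efficacy and prediagnosis activity to later activity; neither trial arm nor baseline GLTEQ is named as a term.

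Baseline values exist for every outcome. Under Effectiveness, the post-diagnosis GLTEQ is collected "as a baseline assessment of physical activity", with FACT-G7 and the self-efficacy item, and the 12-week follow-up repeats the same tools. The primary aim (Aims) concerns moving people who are inactive or moderately active at baseline into a more active category. Recruitment specifies simple randomisation, with no stratification stated.

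Sample size assumes that "23% of cancer survivors are active to the recommended levels for aerobic activity" and that the pack raises this by 18%. The size follows from that: "A sample of 82 participants will be required per arm for a one-tailed test, power of 80% with alpha set at 5" percent. The recruitment target is then raised to 99 in each arm, against an expected loss of one in five.

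**The concern.** A person's activity at baseline is likely to predict their activity 12 weeks later. An analysis that leaves it out carries that person-to-person variation as noise, and under simple randomisation nothing in the design balances it. The eligibility criteria do not exclude people who are already active. In the z test, an active person who stays active therefore counts the same as an inactive person who becomes active, although the aim is about the second.

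The only analyses explicitly described as using before-and-after information are the within-arm tests. They have no control, so time trends, regression to the mean and the effect of being questionnaired all count as improvement. A significant change in one arm and not in the other is easily reported as an effect of the pack, which it does not test. At stake are precision in a trial of modest size and a misleading secondary result.

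**Working it through.** **1. The plan's own figure.** Inputs from Sample size: 23% active, +18 points giving 41%, one-sided 5%, 80% power. The 18% is read as absolute, because a relative increase would need 1,355 per arm. With mean proportion 0.32 and pooled variance under the null:

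n = [1.645·√(2·0.32·0.68) + 0.842·√(0.23·0.77 + 0.41·0.59)]² / 0.18² = (1.085 + 0.545)² / 0.0324 ≈ 82.

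The stated 82 reproduces, and it is the size for the unadjusted z test. A 20% loss from 99 leaves 99 × 0.8 ≈ 79 per arm, where the z test has about 79% power.

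**2. Active status, stratified by baseline status.** Simulation of 40,000 trials: 79 per arm, 23% active at baseline, 23% against 41% active at 12 weeks, one-sided 5%, z test against Mantel-Haenszel with baseline active or not as strata. *Assumption, not in the documents:* the share s of active controls who stay active, varied from 40% to 70%. The share of other controls who become active is then (0.23 − 0.23s)/0.77, for example 9% at s = 70%. The effect is placed either only in people not active at baseline, or as a common odds ratio in both strata.

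| Active controls staying active | z test | Mantel-Haenszel, effect in the not-active only | Mantel-Haenszel, common odds ratio |
|---|---|---|---|
| 40% | 79-80% | 79-80% | 80% |
| 50% | 79% | 81% | 83% |
| 60% | 79% | 83% | 87% |
| 70% | 79% | 87% | 91% |

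Type I error is about 5% for both tests throughout.

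**3. Active status, adjusted for the continuous baseline score.** Simulation of 2,000 trials at 82 per arm, with an assumed latent baseline-to-follow-up correlation ρ. The z test stays near 80%. Logistic regression on arm and baseline score gives about 82%, 86% and 91% at ρ = 0.3, 0.5 and 0.7.

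**4. Continuous scores.** ANCOVA multiplies the variance of the between-arm difference by 1 − ρ², compared with follow-up values alone:

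- ρ = 0.3: 0.91, so 82 per arm acts like 82/0.91 ≈ 90
- ρ = 0.5: 0.75, like 109
- ρ = 0.7: 0.51, like 161

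**5. Chance imbalance.** With 99 per arm and 23% active at baseline, the SD of the between-arm difference is √(2·0.23·0.77/99) = 0.060. The chance of a gap above 10 points either way is about 9%.

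**6. Within-arm tests with no effect of the pack.** Suppose both arms change by the same d, in SDs of change. With n per arm and a two-sided 5% test, one arm is significant with probability p = Φ(d√n − 1.96) + Φ(−d√n − 1.96), and the intervention arm alone with probability p(1 − p). At n = 79:

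| d (assumed) | p | Intervention arm alone |
|---|---|---|
| 0.1 | 14% | 12% |
| 0.2 | 43% | 24% |
| 0.3 | 76% | 18% |

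At n = 82 the last column is 13%, 25% and 17%.

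**The case against.** The strongest reply is that nothing here is invalid. The z test holds its error rate, its sample size was calculated for it, and chance imbalance under simple randomisation is already part of that error rate. The 9% in step 5 is therefore not a bias. All of this stands. Adjustment is an efficiency gain, and at 40% persistence there is almost none from stratifying.

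A reader might infer that within-arm tests replace the comparison between arms. The text does not support that. The lead test is between arms, the within-arm Wilcoxon tests are secondary, and each within-arm test has a between-arm partner. Nothing says that the pack will be judged by comparing significance across arms, so step 6 measures a risk of interpretation and not a stated plan.

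A reader might also infer that every between-arm test ignores baseline. That is too strong. The article does not say whether the Mann-Whitney and t tests use follow-up values or changes. Changes would use baseline in part, but still without adjusting for it.

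Before-and-after looks beyond week 12 follow from the waiting-list design. Controls receive the pack at 12 weeks, so 24-week maintenance has no untreated comparator. This explains those comparisons but does not make their p-values evidence of effect.

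Finally, an unseen analysis plan could add adjustment. The article nevertheless fixes its tests by name, so the point goes beyond detail left for later.

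**Conclusion.** The concern holds as a missed gain in precision plus a risk of misreading. No named between-arm test is stated to adjust for baseline, although the data are collected and the primary aim refers to them.

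For active status, stratifying takes power from about 79% to somewhere between 79% and 87-91%, for 40-70% persistence of active status in controls and 79 retained per arm. For scores, ANCOVA removes 9-49% of the variance at correlations of 0.3-0.7. The documents give neither persistence nor correlation, so these are ranges, and the upper end should not be quoted alone. The 12-25% for an isolated significant intervention arm assumes equal drift of 0.1-0.3 SD in both arms and is highest near 0.2 SD.

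The figures do not show that the trial is underpowered for want of adjustment, or that the planned z test is wrong. The change is worth making because it costs little and brings the analysis closer to the stated aim.

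**What to change.** In Data Analysis, and in the analysis plan if there is one:

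- Base the 12-week conclusion on active status on a baseline-adjusted between-arm estimate: Mantel-Haenszel stratified by baseline GLTEQ category, or logistic regression on arm and baseline GLTEQ reported as a standardised risk difference. Choose one before the outcome data are seen.
- Keep the unadjusted two-proportion z test as a supporting analysis, since the sample size was calculated for it.
- For 12-week GLTEQ score, FACT-G7 and self-efficacy, use ANCOVA on arm and the baseline value of the same measure. If the Mann-Whitney or t tests are kept as support, state whether they use follow-up values or changes.
- Report within-arm changes, including 24-week maintenance, descriptively with estimates and intervals, and say that they do not test the pack.

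The cost is analysis wording only. No new data, visits or participants are needed.

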**Methods:**

This study is a two-arm waiting list randomized control trial with embedded process evaluation. A sample of 99 participants per arm will be recruited by invitation through an email database of cancer survivors held by UK charity Macmillan Cancer Support and an advert placed on the Macmillan Cancer Support Facebook page. Each participant is randomized to receive brief physical activity information and the UK guidelines for physical activity, or brief physical activity information and the revised Move More Pack with supporting Internet-based tools. The intervention and control arm will be followed up at 12 weeks to identify changes in self-reported physical activity, self-efficacy, and HRQOL based on Web-based questionnaires. The control arm will receive the revised Move More Pack at 12 weeks with follow-up at 24 weeks. The intervention arm is followed up at 24 weeks to determine maintenance of reported changes. Subgroup analyses will be completed based on participants’ prediagnosis level of physical activity and baseline self-efficacy as possible predictors of positive changes. Use of each component of the revised Move More Pack will be assessed using a 4-point Likert scale. Semistructured phone interviews will evaluate the use and perceived usefulness of the revised Move More Pack.

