### Self-Efficacy and Self-Identity

Self-efficacy is central in overcoming the barriers faced by cancer survivors in becoming physically active [19]. Self-efficacy is defined in this context as the confidence of a cancer survivor that he or she has the ability and capacity to be more physically active. Self-efficacy has been reported to be a predictor of intentions to change physical activity in cancer survivors [9,20], consistent with the extant general literature on health behavior change [21]. In addition, identifying as a physically active individual has been reported to be an indicator of physical activity engagement, with those cancer survivors who are physically activity before their diagnoses being more likely to be so afterwards [9]. However, physical activity tends to decrease following diagnosis [22] and is unlikely to reverse without intervention. These predictors of physical activity are reported to be consistent across cancer survivors regardless of age, stage, type of cancer, comorbidity, or treatment received [9].

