### Aims

This study aims to investigate the effect of the revised Move More Pack over 24 weeks. It is hypothesized that use of the revised Move More Pack increases physical activity in cancer survivors, and the proportion of cancer survivors who are classified as active over 12 weeks increases with its use, with changes being maintained at 24 weeks. The primary aim is to test the effectiveness of the revised Move More Pack in reclassifying cancer survivors categorized as inactive or moderately active at baseline, to being more active over 12 weeks, with increases maintained at 24 weeks.

The secondary aims include:

Test the effect of the revised Move More Pack on the self-efficacy and health-related QOL (HRQOL) of cancer survivors.Analyze subgroups to elucidate for whom the revised Move More Pack has a positive effect on physical activity, self-efficacy, and HRQOL in the context of prediagnosis levels of physical activity and baseline self-efficacy.Conduct a process evaluation to contextualize the use and perceived usefulness of the revised Move More Pack.

**Table 1 table1:** The theme and behavior change techniques used in the e-newsletters sent to users of the revised Move More Pack.

Newsletter		Stage of change^a^	BCTs^b^ used^c^
**For those active before diagnosis**^d^			
	Month 1	Doing some physical activity	Information about others’ approval; Information about health consequences; Information about emotional consequences; Graded tasks; Social comparison; Goal setting (behavior)
	Month 2	Doing some physical activity	Information about others’ approval; Information about health consequences; Information about emotional consequences; Framing or reframing; Graded tasks
	Month 3	Doing enough physical activity	Information about others’ approval; Social support (unspecified); Self-reward; Action planning
	Month 6	Making physical activity a habit	Self-monitoring; Action planning; Habit reversal; Habit formation
	Month 9	Making physical activity a habit	Self-monitoring; Action planning; Habit reversal; Habit formation; Social support (unspecified)
	Month 12	Making physical activity a habit	Self-monitoring; Action planning; Habit reversal; Habit formation; Social support (unspecified); Self-reward
**For those inactive before diagnosis**^d^			
	Month 1	Inactive and thinking about becoming physically active	Information about others’ approval; Information about health consequences; Information about emotional consequences; Graded tasks; Social comparison

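### The only stated method for the two subgroup factors models who is active after the intervention; as written it does not show in whom the pack works

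*Protocol article*

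**What the plan says.** The Aims section sets a secondary aim: "Analyze subgroups to elucidate for whom the revised Move More Pack has a positive effect on physical activity, self-efficacy, and HRQOL", in the context of prediagnosis physical activity and baseline self-efficacy. The Methods part of the Abstract repeats it: "Subgroup analyses will be completed based on participants’ prediagnosis level of physical activity and baseline self-efficacy as possible predictors of positive changes".

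In Data Analysis, one sentence uses these factors: "The predictors of self-efficacy and prediagnosis physical activity on post-intervention physical activity levels will be assessed by multiple regression analysis". The other methods listed there are a two-proportion z test, Wilcoxon and Mann-Whitney tests, and paired and independent t tests. None of them is tied to subgroups.

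The Introduction (Self-Efficacy and Self-Identity) gives the background on both factors. On self-efficacy: "Self-efficacy has been reported to be a predictor of intentions to change physical activity in cancer survivors". On prior activity, it describes survivors who were "physically activity before their diagnoses being more likely to be so afterwards". It then refers to the two together as predictors of physical activity and reports that they hold across age, stage, cancer type, comorbidity and treatment.

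**The concern.** Asking for whom the pack has a positive effect is a question about effect modification: does the between-arm difference change with the level of the factor? The stated regression has a post-intervention activity level as its outcome and the two factors as its predictors. Without an arm contrast its coefficients are prognostic. They say that confident or previously active people are more active later, which the Introduction already leads one to expect with or without the pack.

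If those coefficients were read as the answer to the aim, the trial could report that the pack works better in previously active or confident survivors when the data show only that such people are more active. This matters in practice because the e-newsletters are tailored to prediagnosis activity, and the results are meant to inform how the pack is distributed.

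The regression also leaves out two of the three outcomes in the aim, self-efficacy and HRQOL.

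**Working it through.** **1. What the stated regression estimates.** Let A be arm (0 or 1, allocated 1:1), X a factor measured at baseline, and Y the outcome:

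Y = μ + τA + βX + γ(A − ½)X + error

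Here β is the prognostic slope averaged over the arms, and γ is the difference in slope between arms, that is, the effect modification. Randomisation makes X independent of A, so:

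- regression of Y on X in both arms together has expected coefficient β;
- regression of Y on X in the intervention arm alone has expected coefficient β + γ/2;
- only the A-by-X term estimates γ.

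If the pack is wholly ineffective (τ = γ = 0), the first two both equal β, not zero.

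**2. Illustration by simulation.** Assumptions, none from the documents: 82 per arm (164 in total), standard normal factor, residual SD 1, constant pack effect of 0.4 SD, 4,000 runs, two-sided 5% tests. The model without interaction was given an arm term, which is more generous than the stated wording. Because arm is in that model, the rejection rate for X does not depend on the size of the constant pack effect.

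| Truth | No interaction, both arms | Intervention arm only | Interaction test |
|---|---|---|---|
| Prognostic only (β = 0.4, γ = 0) | 99.9% | 94% | 4.9% |
| Effect-modifying only (β = 0, γ = 0.5) | 6% | 59% | 88% |

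The rates depend on the assumed coefficients. The direction follows from step 1.

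**3. The plan's own figure.** The article gives no sample size for this analysis, so its primary calculation is reproduced as the base for step 4. Sample size states that "23% of cancer survivors are active to the recommended levels for aerobic activity" and assumes that the pack "will increase the proportion of the sample achieving the aerobic physical activity guidelines by 18" percent. Reading this as percentage points gives 23% against 41%, mean 32%. At one-tailed 5% and 80% power:

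n = [1.645·√(2·0.32·0.68) + 0.842·√(0.23·0.77 + 0.41·0.59)]² / 0.18² = [1.085 + 0.545]² / 0.0324 ≈ 82 per arm, as stated.

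**4. What an interaction test could detect.** Inputs: 79 per arm (99 × 0.8 = 79.2, the planned recruitment less 20%); 32% active; factor split 50/50 (assumption), so 39.5 per cell.

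- Main-effect SE = √(2·0.32·0.68/79) = 0.074.
- Interaction SE = √(4·0.32·0.68/39.5) = 0.148.
- Detectable with 80% power, two-sided 5%: (1.96 + 0.84) × 0.148 ≈ 0.42.
- Detectable with 80% power, one-sided 5%: (1.645 + 0.84) × 0.148 ≈ 0.37.

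Range over the split: with 31/69 (also an assumption) the cells are 24.5 and 54.5, and SE = √[2·0.32·0.68·(1/24.5 + 1/54.5)] = 0.160. The detectable interaction is then about 45 points two-sided or 40 one-sided.

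**5. Power for particular patterns.** With 82 per arm and 23% active among controls in both subgroups (assumption), the SE is the root of the summed cell variances:

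- +27 against +9 points, 50/50 split: SE = √[(0.23·0.77 + 0.50·0.50)/41 + (0.23·0.77 + 0.32·0.68)/41] = 0.142. Then 0.18/0.142 = 1.27, giving power of about 25% two-sided or 35% one-sided.
- +36 against 0 points, 50/50 split: SE = 0.137, power about 75% two-sided or 84% one-sided.
- The same patterns with the larger effect in a 31% subgroup: about 21% and 67% two-sided.

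**The case against.** The strongest reply is that silence is not exclusion. The sentence names a method family, an outcome and two predictors of interest. It does not list the model's terms, and covariates and interactions are commonly left to an analysis plan that is not shown here. This stands: a reader might infer that the plan rules out an arm term or an interaction, and the article does not say so. What can be criticised is what the sentence does fix, namely an activity level as outcome and the two factors as predictors of that level.

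Second, the article never says that this regression is the analysis for the subgroup aim. The Abstract promises subgroup analyses separately, and the across-arm tests could be run within subgroups for all three outcomes. This also stands in part, because the link is an inference. But no such use of those tests is described, and separate tests within subgroups would still not compare the effect between them.

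Third, the self-efficacy sentence quoted from the Introduction concerns intentions, not activity. That is so. The support comes from the later sentence that calls both factors predictors of physical activity.

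Fourth, the 42-point figure applies to a binary outcome and a dichotomised factor with an unsourced split, and to a two-sided test where the plan's sample size is one-tailed. It might be taken for the size of the error, but it is only an illustration of the low power of such an interaction test.

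**Conclusion.** The point holds, with moderate confidence. The only stated method naming prediagnosis activity and self-efficacy estimates prognosis as written and cannot by itself answer the effect-modification aim. It also does not reach self-efficacy or HRQOL as outcomes. On the article's own background, positive coefficients are to be expected from an ineffective pack.

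The documents give no figure for the size of the resulting bias, which equals the unknown prognostic slope. The simulation shows the mechanism under assumed coefficients only. The documents do not support saying that an interaction has been ruled out, or that the primary comparison is affected: the two-proportion test of arms is untouched. This is a secondary aim, and the change should be made before the analysis.

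**What to change.** State how effect modification will be tested. On the randomised 12-week data, for each of physical activity, self-efficacy and HRQOL, regress the outcome on arm, its baseline value, the factor and arm by factor. Report the interaction estimate with its 95% CI, label it exploratory, and base any statement about who benefits on that estimate. The existing regression can stay if it is described as an analysis of predictors of activity.

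Use week 12 because controls receive the pack then, so later data contain no unexposed comparison. Dichotomising the factors is not required; keeping the scores continuous is an option.

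The cost is analysis wording only, since all the variables are already collected at baseline and follow-up. The downside is low power: only very large differences in effect between subgroups are likely to be detected, so a null interaction should not be reported as showing that the pack works equally for everyone.
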